#### Data Collection

Study data were collected using the open-source Open Data Kit platform using questionnaires administered on Android smartphones or tablets [25]. Data were encrypted for storage on the devices and transferred immediately over an encrypted connection to a secure server at NASCOP. The study database was backed up nightly to a secure server at the University of Washington.

#### Data Analysis

We will use log-binomial regression with robust standard errors to assess the proportion of participants with the main outcomes of interest and use multivariate log-binomial and logistic regression to examine the potential predictors of outcomes of interest, including participant demographics, HIV testing history, sexual behavior, and location. We will conduct time trend analyses to examine the changes in proportions with outcomes of interest over time as the APS are scaled up.

### Aim 2: To Determine the Fidelity, Integration, Acceptability, Demand, Technical Efficiency, and Cost of Implementing APS

#### Study Sites

The aim 2 implementation evaluation occurred in (1) Homa Bay and Kisumu HTS facilities and DREAMS sites; (2) selected subcounty and county administrative offices linked to health facilities; and (3) NASCOP’s national administrative offices in Nairobi, Kenya. We included both high-performing and low-performing facilities and covered the range of facility levels from small rural outposts to high-volume urban clinics.

#### Study Participants

HTS providers involved in tracing and HIV testing of partners underwent in-depth interviews (IDIs) with a qualified qualitative interviewer for the evaluation of acceptability of APS, perceived community demand for APS, and implementation fidelity to the APS protocol. The enrolled index participants and male partners who had received APS also underwent IDIs to evaluate the acceptability and perceived demand for APS. Key APS stakeholders, including facility in-charges, county or subcounty AIDS/sexually transmitted infection coordinators, and administrators at NASCOP, were interviewed to evaluate the integration and perceived demand for APS.

#### Study Procedures

HTS providers, index and partner participants, and key APS stakeholders were informed of and invited to participate in the study. Those interested were screened for eligibility and provided consent for an IDI. IDIs were conducted in the language preferred by an experienced qualitative researcher who spoke English, Swahili, and the local languages in a quiet place at a study facility or another location chosen by the participant.

#### Outcomes

Key outcomes for aim 2 included the determination of (1) health facility and individual-level factors that influence fidelity to APS; (2) acceptability, demand, and health system requirements influencing the feasibility of APS; and (3) costs of APS when integrated into existing HTS. Cost metrics included total incremental economic costs of APS, cost per person traced, cost per person HIV tested, and cost per person linked to ART.

#### Data Collection

##### Implementation Fidelity

Although we anticipated some variation in APS implementation across sites, it was difficult to know how contextual differences in the execution of APS procedures would affect outcomes unless we examined how well the implemented intervention matched the intended implementation. We used a conceptual framework for implementation fidelity to identify and describe the key implementation fidelity elements [26].

A convergent mixed methods approach was used to concurrently collect qualitative and quantitative data. A total of two data sources, facility data and staff, were used to triangulate the implementation fidelity to the APS. Facility-level data were collected daily by HTS providers to ascertain the frequency, type, and success of each tracing attempt using structured questionnaires. Measurement of fidelity started at least 12 months after site activation to provide enough time for HTS providers to familiarize themselves with the APS intervention. In addition, as a staggered study started in the 2 counties, with Homa Bay sites initiating 6 months after Kisumu sites, the 12-month period ensured that HTS providers had significant exposure to APS in both counties before assessment.

##### Acceptability of and Demand for APS

We examined APS acceptability among HTS providers, index clients, and male partner participants. We conducted 14 IDIs with HTS providers (same population in the implementation fidelity aim) and 32 IDIs with clients (16 index clients and 16 partners) to address questions related to APS acceptability from 8 purposively selected facilities that vary in patient volume and APS performance. We selected 1 female index who elicited ≤2 male partners and another female index who elicited >2 male partners at each facility in both Homa Bay and Kisumu. Interview guides addressed APS satisfaction, perceived benefits of the intervention, and challenges that may affect delivery or uptake.

To assess demand, we conducted IDIs with 14 HTS providers, 32 clients, and 20 key stakeholders (same population in the integration aim) to assess experiences with provision, administrative oversight, and use of APS intervention activities. Guiding questions were “To what extent is APS likely to be used or supported, and how much demand for APS is perceived to be there in people (general and specific groups) in the community?” In addition, APS delivery statistics provided information on the actual usage of the services.

All IDIs were conducted by a qualified qualitative interviewer using a semistructured interview guide and audio recorded and transcribed for analysis.

##### Integration

We adapted the analytic framework by Grepin and Reich to develop and assess a strategy for integrating APS into existing HIV programs, [27] measure the extent of integration. Integration was measured by the extent of coordination, collaboration, and consolidation, occurring at various levels (policy, organizational, national or regional, and local). We conducted 20 IDIs with purposively selected key NASCOP policy makers, subcounty and county health management team members, facility staff, and community representatives at study initiation and 1 year into APS scale-up to identify opportunities and challenges for both integration within Kenya’s current HIV cascade of care and extent of integration over time. The findings were used to develop metrics to monitor the extent to which integration occurs at each level during APS implementation, along with specific scoring criteria.

##### Cost

We conducted a microcosting and time-in-motion observation of APS activities. Start-up and recurrent cost data were obtained from financial records, including budgets and expense reports from the MOH, PATH-Kenya, and study sites. We collected information on the quantities of inputs and prices of each input used to implement enhanced APS services, including personnel, commodities, and capital goods (such as vehicles, computers, phones, and other equipment). We also obtained budget expense report data on program design, adaptation, and installation related to awareness raising, materials development, training, and the costs of other start-up activities that are essential for expanding the program. The team sought to obtain information directly from the study sites whenever possible. However, if this information was not available, estimates were used from the MOH records of facilities with similar characteristics. Cost data were synthesized using Microsoft Excel spreadsheets.

##### Technical Efficiency of Health System Requirements

Technical efficiency is a relative measure that compares the inputs used (human, technological, and financial) with the outputs attained (number and level of services) [28]. It is designed to assess whether an organization is deploying the right mix of personnel, equipment, supplies, and facilities to produce outputs at the lowest cost. Using data collected from the cost aim, we examined the necessary health system requirements needed to operate APS provision, identify environmental constraints, and determine their technical efficiency. The domains examined were (1) facility-level characteristics (organizational structure, management, governance, decision-making processes, funding sources, training, supervision, incentives, and accountability) and (2) environmental contextual constraints (size of target population and population actually using the services). Determinants of efficiency are those that affect the cost of delivery, which depends on a facility’s performance.

#### Data Analysis

##### Implementation Fidelity

Using a convergent mixed methods approach, we will examine the health facility characteristics (eg, location or staffing) associated with high fidelity to protocol elements and positive implementation outcomes by triangulating facility-level data with qualitative findings from the HTS provider IDIs. IDI audio recordings will be transcribed and analyzed by 2 independent coders using thematic content analysis to determine the key implementation fidelity themes using both deductive and inductive coding [29].

Descriptive statistics will be used to describe the characteristics of participants by county, type, and success of tracing attempts. Categorical variables will be described using counts and proportions, and continuous variables will be described using medians and IQRs. The time needed to conduct tracing attempts will be described using median and IQR and compared with the standard APS protocol to determine the fidelity to the protocol. Pareto charts based on the Pareto principle that 80% of the effects originate from 20% of the causes will be used to determine the tracing attempts through which most clients are successfully traced [30]. Data collected from HTS providers will be used to describe contextual factors.

In the multivariate analysis, successful tracing attempts (coded as either yes or no) will be the outcome of interest. We will consider two levels of data: individual level with clustering at the facility level. Log-binomial generalized estimating equations with exchangeable correlation structure and robust SEs will be used to estimate the relative risks and 95% CIs of successful attempts by the type of tracing attempt (phone vs physical). Variables associated with linking to care in these univariate analyses (*P*<.10) will be included simultaneously in the multivariate model. Moderators will not be included in this multivariate model; however, they will be used to provide context to the results of the quantitative analysis.

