##### APS Procedures

HTS providers called all elicited male sexual partners to inform them of their HIV exposure and offer HIV testing at the facility or a convenient location in the community. Initially, up to three attempts were made to notify the partners by phone; if unsuccessful, or if the female index client did not provide a phone number for the partner, HTS providers physically traced the partners in the community. If unsuccessful, two further attempts were made to notify the partners, either by phone or in-person. Partners were classified as lost to follow-up after six unsuccessful attempts or if a partner refused to meet with an HTS provider.

When implementing APS, HTS providers informed the partners of their potential HIV exposure without identifying the index participant. They asked the partners about their HIV testing history, provided HIV counseling, and offered HIV testing. Partners with a prior HIV diagnosis were asked about their current HIV care, and those who were out of care were counseled about the benefits and locations to access care. If a notification occurred over the phone, partners were encouraged to seek HTS at a study site or offered the opportunity for study staff to conduct a home-based HIV test. For partners who chose to seek HTS at a facility or safe space, the HTS provider who conducted the initial outreach generally contacted the partners via telephone to remind them of their testing appointment, rescheduled appointments as needed, conducted HTS, and documented test results, even if HTS was conducted at nonstudy sites. If HTS was completed at a nonstudy site by the partner, results were obtained via self-report. If a notification occurred as part of a home visit, partners were offered HTS after verbal consent per Kenya national guidelines [24]. When possible, HTS providers accompanied HIV-positive partners to the nearest HIV comprehensive care center for linkage to care.

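### The fidelity regression models whether tracing succeeded, not whether the tracing procedure was followed, so it cannot identify the factors that influence fidelity

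*Protocol article*

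**What the plan says.** The first key outcome of Aim 2 (Outcomes) is to determine the "health facility and individual-level factors that influence fidelity to APS". Aim 2, Data Collection, Implementation Fidelity explains what is meant: the effect of differences between sites could not be understood "unless we examined how well the implemented intervention matched the intended implementation". For this purpose HTS providers recorded daily the "frequency, type, and success of each tracing attempt".

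The intended tracing procedure is given under Aim 1, APS Procedures. "Initially, up to three attempts were made to notify the partners by phone". If these failed, or if no phone number was given, "HTS providers physically traced the partners in the community". Two further attempts by either mode could follow. "Partners were classified as lost to follow-up after six unsuccessful attempts", or after refusal.

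The analysis section on Implementation Fidelity specifies one regression: "In the multivariate analysis, successful tracing attempts (coded as either yes or no) will be the outcome of interest". It is a log-binomial GEE with facility as the cluster, and it estimates the relative risk of success for phone versus physical tracing. The section also plans descriptive statistics, Pareto charts, coded provider interviews and a mixed-methods look at facility characteristics that go with high fidelity. Time spent on tracing is to be "compared with the standard APS protocol to determine the fidelity to the protocol".

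**The concern.** Fidelity, as the article itself describes it, is a property of what the provider did relative to the procedure. Tracing success also depends on whether the partner could be reached. The two can disagree in both directions. Full adherence with an unreachable partner gives a string of failures, and skipping the phone step but finding the partner gives a success.

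The exposure does not close the gap. Under APS Procedures, physical tracing follows failed phone attempts or a missing number, so mode is largely set by the procedure and by how hard the partner is to reach.

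At stake is the reading of a key outcome. Predictors of reachability could be reported as predictors of fidelity, in a study whose purpose is to guide scale-up.

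**Working it through.** **Construct against outcome**

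| Element | Where (protocol article) | Content |
|---|---|---|
| Question | Aim 2, Outcomes | Facility and individual factors that influence fidelity |
| Construct | Aim 2, Data Collection, Implementation Fidelity | Match between implemented and intended intervention |
| Standard | Aim 1, APS Procedures | Number, mode and order of attempts |
| Data | Aim 2, Data Collection, Implementation Fidelity | Frequency, type and success of each attempt |
| Modelled outcome | Aim 2, Data Analysis, Implementation Fidelity | Success, yes or no |
| Modelled exposure | Same | Phone versus physical |

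Frequency and type would show whether the procedure was followed. The outcome uses only success.

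**The article's own figure**

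The cap of six attempts is reproduced as 3 phone + 1 physical + 2 further = 6, if physical tracing counts as one attempt. On the same count, a partner without a phone number has 1 + 2 = 3 described attempts. The article does not say that physical tracing is a single attempt. If it may be repeated, that path can also reach six.

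**Can per-attempt success move against adherence?**

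The article places the data at the individual level within facility but does not make clear whether the unit is the attempt or the partner. Let p_i be the chance that attempt i succeeds given that earlier ones failed, and let tracing stop after at most k attempts.

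- Partner-level success: S(k) = 1 − (1−p_1)(1−p_2)…(1−p_k).
- Expected attempts per partner: A(k) = 1 + (1−p_1) + … + (1−p_1)…(1−p_{k−1}).
- Per-attempt success: S(k)/A(k).

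All p_i are assumptions. Worked case (a), all six attempts: S = 1 − 0.6×0.7×0.8×0.8×0.9×0.9 = 0.782. A = 1 + 0.600 + 0.420 + 0.336 + 0.269 + 0.242 = 2.867. S/A = 0.273.

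| Assumed success, attempts 1 to 6 | Per attempt, stop after 1 | Stop after 3 | All 6 | Per partner, stop after 1 | All 6 |
|---|---|---|---|---|---|
| (a) .40, .30, .20, .20, .10, .10 | 40.0% | 32.9% | 27.3% | 40.0% | 78.2% |
| (b) half of partners .60, half .10, at each attempt | 35.0% | 28.3% | 23.1% | 35.0% | 73.2% |
| (c) .50, .25, .15, .40, .10, .10 | 50.0% | 36.3% | 33.0% | 50.0% | 84.5% |
| (d) constant .30 | 30.0% | 30.0% | 30.0% | 30.0% | 88.2% |
| (e) .15, .15, .15, .60, .30, .30 | 15.0% | 15.0% | 24.4% | 15.0% | 88.0% |
| (f) .25, .15, .10, .60, .20, .20 | 25.0% | 17.9% | 25.3% | 25.0% | 85.3% |

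In (a) to (c), per-attempt success is lower when all six attempts are completed. In (d) it does not change, in (e) it is higher, and in (f) it is about the same as after one attempt and higher than after three. Partner-level success can only rise with more attempts, because each one multiplies the chance of remaining untraced by a factor of at most 1.

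**The case against.** The strongest reply is that the article never names tracing success as the fidelity endpoint. The regression answers a question the study sets itself, phone against physical tracing, and success is the natural outcome for that. Fidelity is approached separately, by triangulating facility-level data with provider interviews. How high fidelity is scored may stand in the full protocol, the analysis plan or the cited framework, none of which is shown.

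Much of this stands. Fidelity is not wholly unexamined, and the phone-versus-physical analysis is worth keeping. But the article does fix the outcome, exposure and model of the one regression under this heading, and these do not address the stated key outcome. Interviews can explain adherence. They do not quantify what predicts it.

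Three stronger readings are tempting, and the article does not support them:

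- **That the plan would rank early-stopping sites above adherent ones.** No site contrast or site score is described, and facility enters only as the cluster. The reversal also needs the attempt as the unit and success that falls over attempts. Scenarios (d) and (e) show it vanishing or going the other way.
- **That time is an empty criterion because no duration is prescribed.** The APS Procedures section is a summary. It is not shown to be the whole of the standard protocol against which time is compared.
- **That the six-attempt rule contradicts the path for partners without a phone number.** This holds only if physical tracing is one attempt, which the article does not state.

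**Conclusion.** The concern holds in a limited form. The regression specified under Implementation Fidelity models a result of tracing and not adherence to the tracing procedure, so it cannot identify the factors that influence fidelity. This conclusion follows from the text alone and needs no assumed probabilities.

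The possible distortion of per-attempt success is conditional, and its size is unknown. Across the assumed scenarios, going from one attempt to all six changes it by between −17.0 percentage points (50.0% to 33.0%) and +9.4 points (15.0% to 24.4%). If the partner is the unit, the distortion does not arise, although success is still not adherence. The point affects one key outcome of Aim 2 and leaves the Aim 1 effectiveness outcomes untouched.

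**What to change.** 1. From the daily tracing logs, derive a partner-level adherence indicator: yes if the prescribed sequence was followed until success, refusal or the last prescribed attempt, otherwise no.
2. Model this indicator on facility and individual factors with the planned facility-clustered GEE, as the quantitative answer to the first Aim 2 outcome.
3. Keep tracing success, with the phone-versus-physical contrast, as a separate implementation outcome, and state whether its unit is the attempt or the partner.
4. Keep time as a descriptive measure alongside adherence.
5. Before scoring, reconcile in APS Procedures the six-attempt rule with the path described for partners without a phone number, so that each partner is scored against the path that applied.

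The cost is a change of analysis wording and one derived variable. Attempt frequency and type are already logged, so no new data are needed. The downside is that partners with incomplete logs cannot be classified; their number should be reported by facility.

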**Methods:**

Our study team from the University of Washington and PATH is integrating APS into 31 health facilities in Western Kenya. We are enrolling females newly diagnosed with HIV (index clients) who consent to receiving APS, their male sexual partners, and female sexual partners of male sexual partners who tested HIV positive. Female index clients and sexual partners testing HIV positive will be followed up at 6 weeks, 6 months, and 12 months postenrollment to assess linkage to care, antiretroviral therapy initiation, and HIV viral load suppression. We will evaluate the acceptability, fidelity, and cost of real-world implementation of APS via in-depth interviews conducted with national, county, and subcounty-level policy makers responsible for HTS. Facility health staff providing HTS and APS, in addition to staff working with the study project team, will also be interviewed. We will also conduct direct observations of facility infrastructure and clinical procedures and extract data from the facilities and county and national databases.

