## Methods

### Study Design

This hybrid type 2 implementation science study [22] has two aims: (1) to determine the effectiveness of APS when integrated within routine HTS and (2) to evaluate the implementation of APS in these settings, including the integration, implementation fidelity, acceptability, demand, and costs of the intervention. The study leveraged existing integrated HIV prevention, care, and treatment platforms from the Afya Ziwani project, the existing President’s Emergency Plan for AIDS Relief–funded and PATH. PATH is a local nongovernmental organization in Western Kenya. HTSs are provided in facility and community settings, including *safe spaces* where DREAMS (Determined, Resilient, Empowered, AIDS-free, Mentored, and Safe) interventions are provided to vulnerable adolescent girls and young women.

The DREAMS program aims to reduce new HIV cases by providing girls and young women at the highest risk of HIV infection and their partners, families, and communities with a tailored, comprehensive, and evidence-informed HIV service package, including HTS. Afya Ziwani provides technical implementation support to health facilities that serve as sites for study enrollment. Nine safe spaces have been created within the catchment areas of health facilities that provide a variety of services, including HTS, by staff for adolescent girls and young women. Excluding the antenatal care clinics, around 50-80 persons test HIV positive each month in larger facilities and 10-20 in smaller facilities, with more than 50% of newly diagnosed individuals being female. In 2018, HIV prevalence in Homa Bay and Kisumu counties was estimated at 19.6% and 17.5%, respectively, in the general population [23]. Therefore, this is a high number of girls and women with HIV who are enrolled in health facilities and linked safe spaces. This study integrated APS into the existing infrastructure of Afya Ziwani in collaboration with county and subcounty health management teams in Homa Bay and Kisumu counties.

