## Results

As of March 2020, we recruited 1724 index clients, 3201 male partners, and 1585 female partners. We completed recruitment for this study and 6-week (2936/2973, 98.75%), 6-month (1596/1641, 97.25%), and 12-month (725/797, 90.9%) follow-up visits. We are now completing the remaining 12-month follow-up visits. Preliminary analyses demonstrate that by scaling up APS, facilities can identify 12-18 new HIV-positive males for every 100 men contacted and tested. This is considerably higher than the average HTS yield in Kenya of <2%. During this period, 21 individuals were ineligible for the APS study because of IPV concerns. Despite this, there have been 35 IPV events related to HTS and APS, which were not due to procedures. Overall, 32 relationships were dissolved during this period.

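### Aim 2 fidelity model: robust SEs with no stated small-sample correction on at most 31 unequal facilities would make the 95% CI for phone versus physical tracing modestly too narrow if run in the ordinary way

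*Protocol article*

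**What the plan says.** The article's Implementation Fidelity section (Aim 2, Data Analysis) fixes the model, working correlation, variance and interval: "Log-binomial generalized estimating equations with exchangeable correlation structure and robust SEs will be used to estimate the relative risks and 95% CIs". The outcome is success of a tracing attempt, the contrast is phone versus physical tracing, and the data structure is "individual level with clustering at the facility level". The section states no alpha, small-sample correction or choice between normal and t quantiles.

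Three other places describe the clusters:

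- **Number.** The Abstract (Methods) speaks of "integrating APS into 31 health facilities in Western Kenya". How many of these contribute to the fidelity model is not stated.
- **Volume.** The Study Design section says that "around 50-80 persons test HIV positive each month in larger facilities and 10-20 in smaller facilities".
- **Mix.** The Aim 2 Study Sites section says that the selection "covered the range of facility levels from small rural outposts to high-volume urban clinics".

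**The concern.** Clustering on facility is sound: it is the top level, and it also absorbs repeated attempts on the same partner. The difficulty is the variance estimator. The sandwich variance is justified for a large number of clusters. With few clusters its expected value falls below the true variance, because fitted residuals are smaller than true residuals, and unequal cluster sizes make this worse. A normal quantile then ignores the uncertainty in the variance itself.

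In a GEE, robust SEs usually means the uncorrected sandwich, commonly paired with 1.96. An analyst following the sentence literally would probably run that. The Discussion lists the comparison of tracing modes among the process measures meant to inform scale-up, and this model supplies its formal inference. The same SEs would presumably also drive the univariate P<.10 screen.

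**Working it through.** The article gives no power, error rate or sample size for this analysis, so there is no figure of its own to reproduce. The question is what coverage the named method would have.

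**Inputs from the article**

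- Clusters: K = 31 at most (Abstract, Methods).
- Volume ratio, large to small facilities (Study Design): 50/20 = 2.5 to 80/10 = 8; at the midpoints 65/15 = 4.3.
- Mean cluster size: the Results section says "we recruited 1724 index clients, 3201 male partners, and 1585 female partners"; male partners per facility = 3201/31 = about 103.

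**Assumed, not in the article**

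- 30% of facilities are large, and records per facility are proportional to volume (coefficient of variation of size about 0.79).
- Success rate 0.5; intracluster correlation (ICC) 0.01 to 0.15.
- Between-facility SD of the mode effect 0 to 0.3.
- One record per partner.

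**Method.** Data were simulated under no effect. Each data set was fitted by log-link GEE with binomial variance, exchangeable correlation and one covariate. The ordinary variance is V = A⁻¹(Σ uₖuₖᵀ)A⁻¹, where uₖ is the score of facility k. Mancl-DeRouen replaces each facility's residual vector rₖ by (I − Hₖ)⁻¹rₖ, where Hₖ is that facility's leverage block. There were 8000 replicates per setting; Monte Carlo SE = √(0.05 × 0.95/8000) = 0.24 points.

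**Quantile alone.** The two-sided t(29) probability beyond 1.96 is 5.97%, so using z instead of t(29) (2.045) accounts for about 1 point.

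**Error rate (%) at nominal 5%, 31 facilities**

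| Setting | Robust, z | Robust, t(29) | Mancl-DeRouen, t(29) | Mean robust SE / true SD |
|---|---|---|---|---|
| Mode, equal sizes, ICC 0.05 | 6.3 | 5.2 | 4.5 | 0.972 |
| Mode, unequal, ICC 0.01 | 7.8 | 6.8 | 5.3 | 0.940 |
| Mode, unequal, ICC 0.05 | 7.5 | 6.6 | 5.3 | 0.952 |
| Mode, unequal, ICC 0.15 | 6.9 | 5.8 | 4.8 | 0.950 |
| Mode, unequal, ICC 0.05, effect SD 0.15 | 7.9 | 6.6 | 5.4 | 0.938 |
| Mode, unequal, ICC 0.05, effect SD 0.3 | 8.4 | 7.1 | 5.9 | 0.928 |
| Facility covariate, half exposed | 6.6 | 5.6 | 4.3 | 0.950 |
| Facility covariate, about a quarter exposed | 10.0 | 8.7 | 5.7 | 0.904 |

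For phone versus physical tracing with unequal sizes, coverage is 100 − 6.9 = 93.1% down to 100 − 8.4 = 91.6%. The smallest excess, about 1.9 points, is more than seven Monte Carlo SEs. The t quantile alone leaves 5.8-7.1%, so the variance correction is needed too.

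**Second set-up.** A separate simulation used a Poisson working variance, normal random intercepts, 26% large facilities, about 1200 partners and 800 replicates. It gave 6.4-8.0% for the mode contrast and 8.1-9.9% for a facility-level covariate with robust SEs and z. Mancl-DeRouen with t(K − 3) gave 4.6-5.2%.

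**Fewer facilities (purely assumed).** With 20 facilities the second set-up gave 9.6% for mode and 12.4% for a facility covariate. The first, with effect SD 0.3 and 2000 replicates, gave about 13% with 14 facilities and 18.5% with 8.

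**The case against.** The strongest reply is that nothing in the article is wrong. Mancl-DeRouen SEs are themselves robust SEs, so the sentence is compatible with the proposed remedy. The variance variant and reference distribution are details that a condensed article commonly leaves to the full protocol or analysis plan, neither of which is shown. This stands. A reader might infer that the investigators chose uncorrected SEs, or that the reported intervals will be too narrow as a matter of fact. The article supports neither; the shortfall follows only if the sentence is carried out in the ordinary way.

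The reply is also right on these points:

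- The monthly counts are persons testing positive, not tracing attempts, so the true cluster sizes in this model are unknown.
- The lowest figure, 6.4% from 800 replicates, has a Monte Carlo interval of about 4.7-8.1% and alone would not exclude 5%. The larger simulation carries the argument.
- The article names no facility-level covariate for this GEE, and it keeps moderators out of the multivariate model. The 8-10% rates therefore describe a possibility. So do the results for 20, 14 or 8 facilities, since 31 is the only count given.
- This is an association analysis with no stated alpha, set beside descriptive and qualitative work. Nothing shows that moving from about 93% to 95% coverage would change a conclusion.

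What does not stand is that the point is empty. The article goes as far as naming a variance estimator, and its usual implementation misses the stated 95% level in a known direction in both set-ups and at every ICC tried.

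**Conclusion.** The point holds in conditional form and at low severity. If the ordinary sandwich with z = 1.96 is used on 31 unequal facilities, the interval for phone versus physical tracing would cover about 92-93% (error about 6.5-8.5%). Both the small number of clusters and their inequality contribute: equal sizes still give 6.3%. The direction is firm. The size depends on the assumed share of large facilities, success rate, ICC and effect heterogeneity. It would grow if clearly fewer facilities contributed or if an unbalanced facility-level covariate entered, but the article establishes neither. The Aim 1 outcomes are not affected by this point.

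**What to change.** In the Implementation Fidelity analysis section, replace *robust SEs* with: *facility-clustered robust SEs with the Mancl-DeRouen small-sample correction and t quantiles on (number of contributing facilities minus number of parameters) degrees of freedom*. Take the parameter count from the model being reported, since screening decides which covariates enter, and state how many facilities contribute. Other bias corrections exist, but only Mancl-DeRouen was checked here. If the full plan already specifies a correction, naming it is enough.

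The cost is one sentence and a software option, with no new data. Intervals become somewhat wider. On the log scale, the t quantile adds 2.045/1.96 = 1.04. If the correction restores the true SD, a further 1/0.952 = 1.05 to 1/0.928 = 1.08 applies, so roughly 10-12% in all at 31 facilities.
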